**Fig. 4 Fig4:**
[figure not shown]
The study flowchart

### Auditing

At each follow-up, the procedures will be checked in the 14 research settings and subjects who return uncompleted questionnaires will be invited to complete them.

### Data collection and management

Patients’ basic information will be collected by GPs with a questionnaire. Patients’ information during follow-up will be accessible in the health records and supplements by questionnaires if necessary. The data from the questionnaires will be generated in each follow-up, the follow-up date will be indicated, and the questionnaires will be signed by the investigators and double-entered into the Epidata3.0 database by two researchers. The interview content from GPs will be recorded by audio and verbally at the same time after getting informed consent. Two researchers will sum up the conversation and extract the key information related to the study aim independently. Disagreements will be resolved through discussion or by a third person. This study has no composition of data monitoring committee (DMC) because other data will be reserved in the information security department as parts of patients’ medical records. After completing the follow-up, we will apply to the Network Information Security Center of Baoshan District and Jing’an District Health Commission. The codes of the CDSS will not be accessible at any time except installation and necessary maintenance. When installing the CDSS, developers will cooperate with the programmers of HIS providers and minimize the risk of data leakage. If there are any bugs or data leakage, all people will stop using the CDSS until the problem is solved and the ethics committee approves resumption. The GPs can contact the developers and researchers at any time if they encounter any difficulties and a response will be given within 24 h. For severe adverse events, researchers will report them to the ethics committee within 24 h. If it is attributed to the CDSS, the ethics committee, and the principal investigator (PI) can terminate prematurely and conduct interim analyses. And we will compensate those who suffer harm in accordance with the Chinese law, if necessary.

### Sample size

A previous study reported that 12.64% of patients with AF received appropriate anticoagulants in community health centers of Shanghai [34]. Intracluster correlation coefficient (ICC) was 0.02 [35], the power (1-β) was 90%, and the double-sided significance (α) was 0.05. In the pilot study, the proportion of appropriate anticoagulation increased to 28% in the intervention group, so we expected the proportion to be 28% in this study. Seven community health centers are in each group and we plan to enroll 30 patients from each community health center in the control group, meaning a sample size of 448, or 498 to allow for a 10% loss to follow-up.

### Statistical analysis

Categorical data will be reported as frequencies and percentages (*n*, %), and a chi-square test will be used to detect any significant differences. Continuous data will be reported as mean ± SD (standard deviation) and compared using a *t*-test if it is on the Gaussian distribution. Otherwise, the data will be reported as the median (IQR (interquartile range)) and compared using the Mann-Whitney *U* test. Linear regression model will be used to compare the continuous data between the distinct groups, considering the interaction of time and allocation. Logistic regression model will be used to detect the effect of the interventions on the primary outcome. Kaplan-Meier (Log-rank test) and Cox proportional hazard models are to be used for the secondary outcomes and safety outcomes. To simplify the analysis, the follow-up time will be recorded as a unit of a month and regardless of start or end. The time will be calculated from this month, if it occurs in the former month; otherwise, it will be calculated from the next month. All outcomes will be evaluated with Mantel-Haenszel statistics and adjusted for the effect of clustering.

Per-protocol (PP) analysis and the intention-to-treat (ITT) analysis will be conducted after filling missing values by multiple imputations. The subgroup analyses will be conducted by whether the CDSS is installed and used in all general clinics or only the AF special consulting room. The sensitivity analyses will be performed by age strata, gender, resident district, and anticoagulants used.

All statistical analyses will be performed with IBM SPSS Statistics, version 26.0 (SPSS Inc) and R (version 4.0.5). A two-tailed *P* < 0.05 will be considered statistically significant.

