Frequency of consultation is defined as the average times of patients in each group seeking medical care due to AF in community health centers.The INR compliance rate in patients with warfarin is defined as the number of patients with AF treated with warfarin whose TTR values exceed 65%, but excluding those whose INR values exceed 5.0 or are less than 1.5 at least twice in 6 months, or exceed 8.0 at least once [30]. For this calculation, INR values within the initial 6 weeks will be deleted and no less than 6-month INR values should be included.Stroke morbidity during follow-up, including ischemic stroke and transient ischemic attack (TIA).Medication satisfaction of patients, assessed with the Chinese version of the patient satisfaction questionnaire (PSQ-18) [31].The GPs’ capability to manage AF, assessed using a self-administered questionnaire, “Knowledge-Attitude-Practice (KAP) questionnaire of community primary care physicians (PCPs) in anticoagulant therapy for non-valvular atrial fibrillation (NVAF) patients” [32], which was developed and validated by Delphi technique and the reliability and validity evaluation were confirmed by empirical research among GPs in Shanghai [33].Cost-benefit analysis. The costs mainly include the time and labor costs caused by the design, installation, and maintenance of the CDSS compared with the control group, the excess time and labor costs led by GPs using the auxiliary tool and the loss of productivity due to patients’ longer visit time caused by using the CDSS.The GPs’ acceptance of and rational and optimal advice on the CDSS. For this part, we plan to conduct semi-structured interviews

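### Consultation frequency is defined as an average, but the plan's rule for non-Gaussian data would summarise skewed visit counts by the median and test ranks, and it does not say which analysis governs this outcome

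*Protocol article*

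**What the plan says.** In the protocol article, Outcomes, the first secondary outcome reads: "Frequency of consultation is defined as the average times of patients in each group seeking medical care due to AF in community health centers". The target is therefore a group mean.

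Statistical analysis sets a two-branch rule for continuous variables. If the data are Gaussian: "Continuous data will be reported as mean ± SD (standard deviation) and compared using a" t-test. If not: "Otherwise, the data will be reported as the median (IQR (interquartile range)) and compared using the Mann-Whitney" test. No outcome is exempted.

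The same section names further methods:
- "Linear regression model will be used to compare the continuous data between the distinct groups, considering the interaction of time and allocation".
- "Kaplan-Meier (Log-rank test) and Cox proportional hazard models are to be used for the secondary outcomes and safety outcomes".
- Mantel-Haenszel evaluation and adjustment for clustering, for all outcomes.

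The section does not assign consultation frequency to any of these.

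**The concern.** The number of AF visits per patient over 12 months is a non-negative integer and is likely to be right-skewed. If it is handled as a continuous variable, it would probably fail a check for normality and fall into the median and Mann-Whitney branch. Two things then change. The reported summary becomes a median, although the outcome is defined as an average. The test becomes a comparison of ranks: it asks whether a patient in one arm tends to have more visits than a patient in the other, which is not the same as whether the average differs.

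At stake is what the trial may say about consultation frequency. A significant rank test could be read as a change in average visits when the averages are the same, and the published median could not be used to recover the average.

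**Working it through.** **The plan's own figure.** The protocol gives no mean, SD or distribution for visits, so there is no visit figure to reproduce. Its only calculation is the sample size for the primary outcome, used here to set the number per arm. Inputs (Sample size section): 12.64% v 28%, ICC 0.02, two-sided α 0.05, power 90%, 7 centres per arm, 30 patients per control centre.
- Variance, control: 0.1264 × 0.8736 × (1 + 29 × 0.02) / 210 = 0.000831.
- Variance, intervention with 34 per centre: 0.28 × 0.72 × (1 + 33 × 0.02) / 238 = 0.001406.
- z = 0.1536 / √0.002237 = 3.248. Subtracting 1.96 leaves 1.288, a power of 90.1%.
- Total: 7 × 30 + 7 × 34 = 448. With 10% loss: 448 / 0.9 = 497.8, rounded up to 498.

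Both stated totals are reproduced. For the illustration, 448 / 2 = 224 per arm.

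**Assumptions of the illustration (not from the documents).** Negative binomial visit counts with mean 6 in both arms, independent patients, 2000 simulated trials per setting, two-sided 5% tests. The variance is mean + mean²/k, where k is the dispersion parameter:
- k = 0.8: 6 + 36/0.8 = 51
- k = 1: 6 + 36/1 = 42
- k = 1.5: 6 + 36/1.5 = 30
- k = 2: 6 + 36/2 = 24
- k = 3: 6 + 36/3 = 18

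**Why equal means can give unequal ranks.**
- k = 1: P(X ≤ x) = 1 − (6/7)^(x+1). This is 0.460 at x = 3 and 0.537 at x = 4, so the median is 4.
- k = 2: P(X = x) = (x+1) × 0.0625 × 0.75^x. The cumulative probability is 0.466 at x = 4 and 0.555 at x = 5, so the median is 5.

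The mean is 6 in both cases, yet the medians differ.

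**Rejection rates with equal means of 6.** Ranges cover repeated runs.

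| Dispersion k, arm v arm | Variances | Mann-Whitney |
|---|---|---|
| 1 v 1, or 2 v 2 | equal | about 4-5% |
| 1 v 1.5 | 42 v 30 | about 17-19% |
| 1 v 2 | 42 v 24 | 37-39% |
| 0.8 v 3 | 51 v 18 | 83-85% |

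Welch's t rejected in about 4-6% of trials, so at this sample size the mean comparison holds its level on these skewed counts.

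**When the means differ (4 v 5).**
- Same dispersion (k = 4 in both arms): Mann-Whitney is significantly higher in 89% of runs and the t-test in 93%. They agree.
- Very different dispersion (k = 4 v 0.8; variances 4 + 16/4 = 8 and 5 + 25/0.8 = 36.25): the mean difference and the rank effect have opposite signs in 81% of runs. Mann-Whitney is significantly lower in 17%, and the t-test significantly higher in 63%.

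**The case against.** The strongest reply is that the protocol never commits visits to the rank test. The rule is conditional on non-normality, it speaks of continuous data, and a visit count may not be meant. The linear regression in the next sentence works on means and carries no normality switch. Patients are followed month by month, so visits could be analysed over time in that model. All outcomes are also to be adjusted for clustering, so a plain Mann-Whitney cannot be the final analysis as written.

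This stands in part. The rank test is not certain to be used. What remains is that two analyses with different targets could both claim this outcome, only one matches its definition, and the text does not choose. Kaplan-Meier and Cox address time to an event, not visit counts, and do not settle it.

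A second reply is that the inflated rejection needs different spread in the two arms, and no passage gives data on spread. This also stands. That a decision-support tool might make visits more regular is plausible but conjectural, and the larger percentages come from the assumed inputs.

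A reader might also infer that the rule spoils the cost-benefit analysis. The text does not support that. It states no average or total as the cost target and no two-sample test of costs. It lists components: "The costs mainly include the time and labor costs caused by the design, installation, and maintenance of the CDSS compared with the control group" covers system-level items with no patient distribution to rank, and "the excess time and labor costs led by GPs using the auxiliary tool" is incremental by definition. The method of the economic analysis may reasonably sit in the full protocol or analysis plan.

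**Conclusion.** The point holds for consultation frequency: the outcome is defined as an average, and the general rule would replace that average by a median and a rank test if the counts are treated as continuous and are skewed. The plan does not state which analysis takes precedence.

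The size depends on a quantity that the documents do not give. With equal dispersion nothing is lost: about 4-5% rejection under equal means. With the moderate differences assumed here, it rises to about 17-19% (variances 42 v 30) and 37-39% (42 v 24), against a nominal 5%. These figures assume negative binomial counts, equal means of 6, 224 per arm and no clustering. They show the mechanism and do not predict this trial's error rate.

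A reader might infer that the result is likely to point the wrong way. That goes too far: a reversal needs strongly different distribution shapes in the two arms and, apart from chance, does not arise when the shape is shared.

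Only a secondary outcome is touched. The primary outcome is binary and analysed by logistic regression, so neither it nor the sample size is affected.

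**What to change.** In Statistical analysis, exempt consultation frequency from the normality switch and name its analysis. Compare it on the mean scale, as a mean difference or rate ratio with a 95% CI, from a cluster-adjusted count or linear model or from a bootstrap that resamples centres. Show the median (IQR) as description only. State that this analysis governs the outcome. If any person-level cost item is compared between arms, apply the same rule to it.

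The cost is a change of wording in one paragraph and slightly more analysis work. Design, recruitment and data collection are unchanged.

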### Outcomes

The primary outcome is the proportion of antithrombotic treatment prescriptions, in agreement with recommendations in the AF guidelines. It is defined as the agreement rate between the doctor’s anticoagulation prescriptions for newly diagnosed patients and the system’s recommendations, including prescribing anticoagulation drugs or recommending referral to superior hospitals for patients with anticoagulation indications, and refraining from anticoagulation for patients without such indications or with contraindications.

The safety outcomes, such as the incidence of bleeding events, all-cause mortality and in-patient events related to AF or AF complications will be reported. Referring to the Guideline of stroke prevention in Chinese patients with atrial fibrillation (2017), bleeding events are classified as minor and major bleeding [4].

The secondary outcomes contain seven items:

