### Enrollment and follow-up

GPs will be first enrolled, trained, and invited to complete the same KAP questionnaire on antithrombotic treatment three times before and after the training and at the end of the study. In the last month, one GP in each community health center of the intervention group will be randomly selected for a semi-structured interview. After training, GPs can enroll patients with AF that meet all the inclusion criteria and none of the exclusion criteria into this study, after signing the informed content. The follow-up will last for 12 months. Within the first week and the fourth, eighth, and twelfth months after enrolling, patients will be required to finish the PSQ-18 questionnaires. Patients will be contacted by telephone at the last week of a month or the first week of the next month, if they do not revisit their doctors in that month. One free INR point-of-care testing (POCT) collecting finger-stick blood will be provided to patients who complete all the 1 year time’s follow-up and the reasons for patients not finishing the study will be collected if possible. The study flowchart is shown in Fig. 4.

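### The plan names no within-person correlation for the repeated PSQ-18 and KAP scores, and separately assigns survival methods to secondary outcomes that, apart from stroke/TIA, are not event times

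*Protocol article*

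**What the plan says.** Repeated scores. Under Enrollment and follow-up, the patient satisfaction schedule is: "Within the first week and the fourth, eighth, and twelfth months after enrolling, patients will be required to finish the PSQ-18 questionnaires". The GPs are invited to "complete the same KAP questionnaire on antithrombotic treatment three times before and after the training and at the end of the study". That makes four PSQ-18 scores per patient and three KAP scores per GP.

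Model for scores. Under Statistical analysis, continuous data go to a t-test or Mann-Whitney test, and then: "Linear regression model will be used to compare the continuous data between the distinct groups, considering the interaction of time and allocation". No mixed model, GEE or within-person covariance is named.

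Clustering. The same section adds: "All outcomes will be evaluated with Mantel-Haenszel statistics and adjusted for the effect of clustering". It gives neither the level of clustering nor the method of adjustment.

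Survival methods. The same section states: "Kaplan-Meier (Log-rank test) and Cox proportional hazard models are to be used for the secondary outcomes and safety outcomes". No restriction to event outcomes follows. Under Outcomes, "The secondary outcomes contain seven items", and the first is worded: "Frequency of consultation is defined as the average times of patients in each group seeking medical care due to AF in community health centers".

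**The concern.** There are two separate problems.

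First, a time term in the model means that several scores from the same person enter it together. A linear regression with no further qualification takes residuals as independent. Scores from one patient or one GP are positively correlated, so the standard errors would be off in a direction that depends on the contrast: too small for a group difference averaged over visits, too large for a change over time compared between groups. Satisfaction and GP capability are the outcomes exposed to this.

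Second, read literally, the survival sentence covers outcomes that have no event time. It gives PSQ-18 and KAP two methods that cannot both apply. Consultation frequency and INR compliance also receive a method that does not match their definition. An analyst would have to choose a method after the data are in, which a plan should prevent.

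**Working it through.** **Is there a planned figure to reproduce?** Not for these outcomes. The only sample size in the article is 448, or 498 with 10% loss, and it concerns the primary outcome. It reproduces closely: 143 per arm for 12.64% against 28% at 90% power and two-sided 0.05, times 1 + (30 − 1) × 0.02 = 1.58, gives 452 in total (440 with unpooled variance). 448 / 0.90 = 497.8, rounded up to 498. It does not bear on this point.

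**Part 1: repeated scores treated as independent**

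Inputs: k = 4 for PSQ-18 and k = 3 for KAP (Enrollment and follow-up). The within-person correlation ρ is not given, so 0.3, 0.5 and 0.7 are assumed, equal between all visits. Centre clustering is left out here.

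*Group effect pooled over visits.* True SE / naive SE = √(1 + (k − 1)ρ). Type I error at nominal 5% = 2 × [1 − Φ(1.96 / ratio)].

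| ρ | PSQ-18 ratio | Type I error | KAP ratio | Type I error |
|---|---|---|---|---|
| 0.3 | √1.9 = 1.38 | 0.155 | √1.6 = 1.26 | 0.121 |
| 0.5 | √2.5 = 1.58 | 0.215 | √2.0 = 1.41 | 0.166 |
| 0.7 | √3.1 = 1.76 | 0.266 | √2.4 = 1.55 | 0.206 |

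*Time-by-allocation term.* Naive SE / true SE = 1 / √(1 − ρ), whatever k is. Type I error = 2 × [1 − Φ(1.96 / √(1 − ρ))]. If a correct analysis had 80% power (an assumption; the article states none), the estimate divided by its true SE has mean 2.80 and SD 1. It must exceed 1.96 / √(1 − ρ), so power = Φ(2.80 − 1.96 / √(1 − ρ)).

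| ρ | Naive / true SE | Type I error | Power instead of 80% |
|---|---|---|---|
| 0.3 | 1.20 | 0.019 | Φ(2.80 − 2.34) = 0.68 |
| 0.5 | 1.41 | 0.006 | Φ(2.80 − 2.77) = 0.51 |
| 0.7 | 1.83 | 0.0003 | Φ(2.80 − 3.58) = 0.22 |

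The two directions do not conflict: they belong to different contrasts of one model. For a difference at a single visit, k = 1 and the first ratio is 1, so within-person correlation drops out and centre clustering remains.

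**Part 2: secondary outcomes against the survival sentence**

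| Secondary outcome (Outcomes section) | Type | Event time? |
|---|---|---|
| Consultation frequency | Count, averaged by group | No |
| INR compliance on warfarin | Proportion of patients | No |
| Stroke, including TIA | Event during follow-up | Yes |
| PSQ-18 | Repeated score | No |
| KAP | Repeated score | No |
| Cost-benefit | Economic analysis | No |
| GP acceptance of the CDSS | Interviews | No |

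One of seven fits. The safety outcomes (bleeding, death, AF-related in-patient events) can all be analysed as event times.

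**The case against.** The article never says that repeats are treated as independent. The time-by-allocation term signals a longitudinal analysis, a condensed article may leave the covariance structure to a fuller document, and adjustment for clustering is promised for every outcome. Patients and GPs are nested in centres, so centre-level robust standard errors would also absorb within-person correlation. This stands, and it limits the point. A reader might infer that the standard errors are certainly wrong; the text does not support that. What remains is that the named model does not fit the data schedule, that the clustering sentence names no method suited to a continuous score, and that robust errors with 14 centres would need a small-sample correction.

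The large type I error belongs to a pooled group effect, whereas the plan names the interaction, for which the naive analysis is conservative. That also stands, so the two results are kept apart above.

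On survival methods, chi-square, t-test and regression are already given for other data types, and the sentences that follow concern follow-up time in months. Event outcomes were probably intended, and nobody would fit a Cox model to interviews. The likely intention does not change the wording, which is unrestricted. But the fault is one of applicability; it would be wrong to infer from it that any standard error is misstated.

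A reader might also infer that the first PSQ-18 follows CDSS use, so that the interaction removes an early effect. This is plausible, but the article only places the questionnaire within a week after enrolment and does not give the order. Nor does it say that a slope alone will be tested.

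**Conclusion.** The point holds as two corrections to stated methods.

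The linear regression for PSQ-18 and KAP needs a stated within-person correlation. The errors are conditional on repeats being treated as independent and on the assumed equal correlation of 0.3 to 0.7. For PSQ-18 pooled over visits, the SE is then 1.38 to 1.76 times too small and type I error is about 16% to 27%; for KAP, 1.26 to 1.55 times and about 12% to 21%. For time by allocation the analysis loses power and does not gain false positives.

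The survival sentence must be restricted, because six of the seven secondary outcomes are not event times. This conclusion needs no assumption.

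Only secondary and safety analyses are touched. The change should be made before analysis.

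**What to change.** - **PSQ-18 and KAP:** use a linear mixed model, or GEE, with patient (PSQ-18) or GP (KAP) and centre levels, visit as a category, arm by visit, and district as a fixed effect because randomization was stratified by location. Apply a small-sample correction for 14 centres. Report the month-12 difference for PSQ-18 and the end-of-study difference for KAP, with KAP adjusted for the pre-training score.
- **Consultations:** a clustered count model, for example negative binomial, with log follow-up time as offset.
- **INR compliance:** a clustered binary model among patients on warfarin.
- **Log-rank and Cox:** limit to stroke/TIA, bleeding, death and AF-related in-patient events, with centre clustering accounted for.
- **Mantel-Haenszel:** limit to categorical outcomes, and name the clustering method for each type of outcome.

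Other valid models exist; what matters is that one is named per outcome. The cost is wording and some extra analysis work. No new data are needed, and R is already among the planned software.

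### The primary logistic model names no covariate or stratum; pre-specifying the patient's indication class, which decides what counts as agreement, would be a cheap gain in power and a guard against case-mix differences

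*Protocol article*

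**What the plan says.** Under Outcomes, the primary outcome pools two opposite tasks. For a patient with an indication, agreement means prescribing an anticoagulant or recommending referral. For the others it means "refraining from anticoagulation for patients without such indications or with contraindications".

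Under Statistical analysis, the model is described in one sentence: "Logistic regression model will be used to detect the effect of the interventions on the primary outcome". The same section adds Mantel-Haenszel statistics for all outcomes, with strata not named, and an adjustment for clustering. Subgroups are defined by where in the centre the tool is installed. Of the other factors it says: "The sensitivity analyses will be performed by age strata, gender, resident district, and anticoagulants used". Indication class is in none of these lists.

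Randomisation was stratified by location only. Administrators were told their centre's allocation, and neither researchers, participants nor analysts are blinded. GPs enrol patients after their training, which in the intervention arm includes training on the tool.

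**The concern.** The planning baseline is that "12.64% of patients with AF received appropriate anticoagulants in community health centers of Shanghai", and the Background describes AF as usually ignored in community centres. If not anticoagulating is the usual course, the same inaction scores as disagreement in an indicated patient and as agreement in a non-indicated one. Class would then explain a good part of the outcome variance, and a centre with more non-indicated patients would show higher agreement with no difference in care.

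Two things are at stake. A model without class leaves that variance in the error term. And with only seven centres per arm and open enrolment after allocation, the class mix may differ between arms, so the crude contrast may partly reflect case mix. Naming the covariate in advance matters more here because the analysts are unblinded.

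**Working it through.** **Inputs from the article (Sample size).** Control 12.64%; intervention 28% ("so we expected the proportion to be 28% in this study"); "Intracluster correlation coefficient (ICC) was 0.02"; "the double-sided significance (α) was 0.05"; power stated as 90%; seven centres per arm; 30 patients per control centre; 448 patients, or 498 after 10% loss.

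**The plan's own figure.** Seven control centres of 30 give 210 patients. The remaining 448 − 210 = 238 make 34 per intervention centre. With design effects 1 + 29 × 0.02 = 1.58 and 1 + 33 × 0.02 = 1.66:

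- Variance of the difference = 0.1264 × 0.8736 × 1.58/210 + 0.28 × 0.72 × 1.66/238 = 0.000831 + 0.001406 = 0.002237; SE = 0.0473.
- 0.1536/0.0473 = 3.25. Normal approximation: power 90.1%. Noncentral t on 14 − 2 = 12 df: 84.6%.
- 448/0.9 = 497.8, so 498.

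Both 448 and 498 reproduce with no covariate in the model.

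**Power with class in the model.** The article gives neither class shares nor class-specific rates, so these are assumptions: a share w of 5–10% non-indicated; their agreement q of 70–90% in both arms; overall rates held at 12.64% and 28%. The rate in indicated patients is then (overall − wq)/(1 − w). The residual variance per arm is wq(1 − q) + (1 − w) × p(1 − p), with p the rate in indicated patients. The ICC of 0.02 is applied to it and 12 df are kept.

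- w = 5%, q = 70%: indicated rates 9.6% and 25.8%; residual variances 0.0931 and 0.1923 (unadjusted 0.1104 and 0.2016); SE 0.0452; power 88%.
- w = 10%, q = 90%: indicated rates 4.0% and 21.1%; residual variances 0.0439 and 0.1589; SE 0.0379; power 96%.

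So about 85% becomes 88–96%, a gain of 3 to 11 points.

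**A second set of assumptions.** Take 60–90% indicated, control agreement of 5–12.64% among them, a common odds ratio, 224 per arm and the normal approximation. Class then explains 0 to 33% of the outcome variance, and power goes from 89.9% to 89.9–97.7%. The gain vanishes when agreement is the same in both classes.

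**Case mix.** With no true effect, a 10-point difference between arms in the non-indicated share shifts the crude difference by 0.10 × (q − p).

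- With p = 12.64%: 0.10 × (0.70 − 0.1264) = 5.7 points to 0.10 × (0.90 − 0.1264) = 7.7 points.
- With p solved from the overall rate as above: 6.0 to 8.6 points.

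That is roughly 6–8 points against a planned effect of 15.4.

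**How large an imbalance chance would produce.** SD of the arm difference in share = √[2w(1 − w)(1 + 31ρ)/224], with 32 per centre and an assumed ICC ρ for class of 0.02–0.10. For w = 5–10% this is 2.6 to 5.7 points, so a 10-point imbalance is 1.7 to 3.8 SD.

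**The case against.** **Silence is not exclusion.** The article does not call the model unadjusted, and Mantel-Haenszel methods are stratified by nature, so class could be one of the unnamed strata or could stand in a fuller document that is not shown. This stands: a reader might infer that the plan rejects adjustment for class, and the text does not support that. What remains is a recommendation about method, not a complaint that a covariate list is missing.

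**No stated power is lost.** A reader might infer an underpowered trial. But the planned 448 already assumes an unadjusted comparison. The gap between 90% and 85% comes from using 12 df, not from omitting class.

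**Chance imbalance is not bias.** Over randomisation it adds variance, and part of that is already carried by the ICC and the clustering adjustment. Bias needs recruitment that differs between arms by class. The open design permits this, but the documents do not show it.

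**The magnitudes rest on assumed inputs.** This also stands, and it limits which inputs are admissible. For example, 20% non-indicated at 80% agreement, with 12.64% in the indicated, gives an overall control rate of 0.8 × 0.1264 + 0.2 × 0.80 = 26%, which departs from the plan. If 12.64% is the overall rate, a class agreeing at 80% cannot exceed 0.1264/0.80 = 15.8% of patients. Nor is class the strongest predictor by construction: it fixes which action counts as agreement, not how often that action occurs. Referral also counts for indicated patients, and its frequency under usual care is not given.

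**Class may depend on arm.** In the intervention centres the tool itself prompts the collection of tests and history, so a class derived from the scored consultation could be affected by allocation, and adjusting for it could introduce bias. This is a sound warning about how class is defined. Using records dated before that consultation meets it, and eligible patients must have been registered with their GP for at least a year. Since the outcome concerns newly diagnosed patients, some records will still be insufficient.

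**Conclusion.** The point holds as an improvement worth making, not as an error in the plan. The article scores agreement by a rule that depends on indication class and names class in no adjustment, stratification, subgroup or sensitivity list. Naming it in advance is the better method.

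Under the plan's own overall rates the benefit is 3 to 11 power points on 12 df, given 5–10% non-indicated patients with 70–90% agreement. It is nil if the classes agree equally often. Protection against case-mix differences is a second benefit: roughly 6–8 points of crude difference per 10 points of imbalance, although with these shares chance alone would more typically produce an imbalance of about 3–6 points (one SD). The documents support neither a shortfall against the stated 90% nor a finding that the comparison is biased.

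**What to change.** Under Statistical analysis:

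- Pre-specify indication class (indicated; not indicated or contraindicated) as a fixed covariate in the cluster-adjusted primary logistic model and as a stratum of the Mantel-Haenszel analysis.
- Derive class by one rule, applied identically in both arms, from record data dated before the scored consultation, with a separate category where class cannot be determined.
- Report a standardised risk difference as the effect measure, with class-specific agreement rates by arm beside it.

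Cost: about a sentence of plan text, one extra model term and some work to derive class from records; the sample size does not change. The adjusted odds ratio becomes conditional on class. Under the second set of assumptions above, the planned marginal odds ratio of (0.28/0.72)/(0.1264/0.8736) = 2.69 corresponds to a conditional one of 2.69 to 4.90, which is why the standardised risk difference is needed.
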